**Fig. 1 Fig1:**
[figure not shown]
Study design of the HIBISCUS trial. ECOG Eastern Cooperative Oncology Group, IS Interrupted Suturing, CBS Continuous Barbed Suturing

### Patient and public involvement

Patients and the public were not involved in the design, conduct, reporting, or dissemination plans of this research, consistent with the SPIRIT 2013 recommendations.

### Study population

Patients with a pathological diagnosis of colorectal cancer who are scheduled to undergo robotic or laparoscopic surgery in which a midline incision will be used for specimen extraction will be eligible for inclusion.

### Inclusion criteria

Patients diagnosed with colorectal cancer and scheduled for elective laparoscopic or robotic-assisted surgery requiring a small midline incision will be asked to provide informed consent at the outpatient clinic or hospital prior to surgery. Eligible patients must meet all of the following criteria:

Scheduled to undergo elective laparoscopic or robotic-assisted colorectal surgery requiring a mini-laparotomy with a small midline incision for specimen extraction.Histologically confirmed diagnosis of colorectal cancer (adenocarcinoma, mucinous carcinoma, signet-ring cell carcinoma, or adenosquamous carcinoma) based on preoperative biopsy.Eastern Cooperative Oncology Group (ECOG) performance status of 0–2.Age 20–85 years at the time of enrollment.No planned stoma creation.No history of neoadjuvant chemotherapy or radiotherapy.Provision of adequate study explanation and written informed consent.

### Exclusion criteria

Presence of any of the following severe comorbid conditions:
⚬ Active systemic infection requiring treatment.⚬ Fever ≥ 38.0℃ at the time of enrollment.⚬ Ongoing systemic administration (oral or intravenous) of steroids or other immunosuppressive agents.⚬ Uncontrolled diabetes mellitus.⚬ Unstable angina (onset within the past 3 weeks or recent worsening of symptoms) or history of myocardial infarction within the past 6 months.⚬ Uncontrolled valvular disease, dilated cardiomyopathy, or hypertrophic cardiomyopathy.
Peritoneal dissemination.History of midline laparotomy with a current or previous IH.
*Note: A history of midline laparotomy alone is not an exclusion criterion.*
Psychiatric disorders or symptoms that interfere with daily activities.Pregnancy or possibility of pregnancy.Any other condition deemed inappropriate for participation in this study by the principal or sub-investigator.

### Registration procedure

The Research Electronic Data Capture (REDCap) platform is used as the electronic data capture system for this trial and is managed by the Data Management Center of Nagoya City University. After written informed consent is obtained, eligible patients are registered in the REDCap system. The registration record includes the study identification number, date of birth, sex, responsible physician, and confirmation of eligibility. Secure access to the system is ensured by assigning each participating institution a unique login ID and password with restricted user permissions.

### Randomization procedure

Randomization is performed within the same REDCap platform using a stratified block randomization method. Stratification factors include participating institution, body mass index (BMI; <25 kg/m² or ≥ 25 kg/m²), and sex (male or female), as BMI and sex are established risk factors for incisional hernia and may influence abdominal wall characteristics and wound healing. A fixed block size is used within each stratum to ensure balance between the treatment groups. Once patient eligibility is confirmed in REDCap, allocation to either the continuous barbed suturing (CBS) group or the interrupted suturing (IS) group is automatically generated by the system. This automated process ensures allocation concealment and minimizes the potential for investigator-related bias in treatment assignment.

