## Methods/design

### Trial design

The HIBISCUS trial is designed as a prospective, multicenter, open-label RCT comparing CBS with IS.

The HIBISCUS trial is a multicenter, prospective, open-label, randomized controlled study comparing continuous barbed suturing with interrupted monofilament suturing for fascial closure of mini-laparotomy incisions (Fig. 1). The study is conducted across six participating institutions in Aichi Prefecture, Japan. Eligible adults with colorectal cancer undergoing elective laparoscopic or robot-assisted resection will be randomized in a 1:1 ratio to continuous closure using a barbed absorbable suture (STRATAFIX Symmetric PDS Plus; bite width of 5 mm and stitch spacing of 5 mm) or interrupted closure using a monofilament absorbable suture (PDS Plus; bite width of 8 mm and stitch spacing of 8 mm). This study is registered in the Japan Registry of Clinical Trials (jRCT1040250129). Registration date: November 21, 2025. Ethical approval was obtained from the Certified Review Board of Nagoya City University, and the protocol has been reviewed and approved by the institutional review boards of all participating hospitals. Patients will be recruited from six hospitals in Aichi Prefecture. The planned enrollment period is 1.5 years, followed by a 1.5-year follow-up period, resulting in a total maximum follow-up duration of 3 years. The study protocol was developed in accordance with the Standard Protocol Items: Recommendations for Interventional Trials (SPIRIT) 2013 guidelines.

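### In an open-label trial, a fixed block size within institution strata leaves some upcoming allocations deducible, so automated release does not by itself ensure allocation concealment

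*Protocol article*

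**What the plan says.** Four statements in the protocol article bear on this point.

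- **Masking and ratio** (Trial design). The trial is a "prospective, multicenter, open-label RCT comparing CBS with IS", and patients "will be randomized in a 1:1 ratio to continuous closure using a barbed absorbable suture" or to interrupted closure.
- **Strata** (Randomization procedure). "Stratification factors include participating institution, body mass index" (two categories) and sex. Trial design adds: "The study is conducted across six participating institutions in Aichi Prefecture, Japan".
- **Blocks** (Randomization procedure). "A fixed block size is used within each stratum to ensure balance between the treatment groups". The size is not given.
- **Concealment** (Randomization procedure). The system generates the allocation once eligibility is confirmed, and the section concludes: "This automated process ensures allocation concealment and minimizes the potential for investigator-related bias in treatment assignment".

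The section Registration procedure places written consent and registration before allocation. The exclusion criteria end with a discretionary item left to the judgement of the principal or sub-investigator.

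**The concern.** Central release protects the list. It does not protect against inference from assignments already made, and in an open-label trial those assignments are known at the site. Because institution is a stratification factor, each stratum's sequence runs wholly within one hospital, which sees all of it. Because the block size is constant within the stratum, the sequence returns to balance at regular intervals. Once one arm's places in a block are used up, the rest of that block is known.

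Selective enrolment is what is at stake. Someone who knows the next assignment can act before registration, for instance through the discretionary exclusion. The effect could go either way. Holding back high-risk patients when interrupted suturing is next would leave relatively more of them in the barbed-suture arm and work against the superiority hypothesis. Holding them back when barbed suturing is next would favour it. Events are few: at 192 per group the planning rates imply 192 × 0.115 ≈ 22 hernias against 192 × 0.039 ≈ 7, so a modest shift in who enters which arm could matter.

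Preferences between the techniques are plausible. The article reports that the coordinating university already uses the barbed suture and that 90% of surveyed institutions use interrupted closure. This does not suggest misconduct.

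**Working it through.** The article gives no block size and no predictability figure, so there is nothing of its own to reproduce here. Its sample size of 192 per group is reproducible and is not affected.

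**Inputs from the article.** Six institutions, two BMI categories, two sexes, 1:1 allocation, target of 422 patients, fixed block size, open label.

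**Strata.** 6 × 2 × 2 = 24 strata, four per site. On average this is 422 / 24 ≈ 17.6 patients per stratum and 422 / 6 ≈ 70 per site.

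**Assumptions.** The block size *b* is one of 2, 4, 6 or 8. Staff know or have inferred *b* and follow each of their four sequences correctly.

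**Share known with certainty.** An allocation is certain when one arm's *b*/2 places in the current block are already used. Enumerating all equally likely orderings gives an expected share of 1 / (*b*/2 + 1). For *b* = 4 there are six orderings. Two of them (AABB, BBAA) have two certain places each, and the other four have one each. That is 2×2 + 4×1 = 8 certain places out of 6×4 = 24, or 33%.

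**Best-guess success.** The guesser always names the arm with more places left and tosses a coin when they are equal. For *b* = 4 the four positions are guessed correctly with probability 1/2, 2/3, 2/3 and 1, so the mean is 2.833 / 4 = 71%. Simple randomization gives 50%.

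| Fixed block size (assumed) | Certain in advance | Of 422 patients | Best-guess success |
|---|---|---|---|
| 2 | 50% | 211 | 75% |
| 4 | 33% | about 141 | 71% |
| 6 | 25% | about 106 | 68% |
| 8 | 20% | about 84 | 67% |

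These figures are for complete blocks. A stratum that stops partway through a block has slightly fewer certain places: simulating 18 patients per stratum with a fixed block of 4 gives about 30% certain and 69% guessed.

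**After the change.** The simulation had 18 patients per stratum and randomly varying block sizes. The guesser knew the set of possible sizes and updated optimally after each assignment.

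| Varying sizes | Certain in advance | Best-guess success |
|---|---|---|
| 4, 6 | about 6% | about 68% |
| 2, 4, 6 | about 4% | about 70% |
| 4, 6, 8 | about 2% | about 67% |

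Like for like at 18 patients per stratum, moving from a fixed block of 4 to sizes 4 and 6 takes the certain share from about 30% to about 6%. Best-guess success barely moves, from 69% to 68%.

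**The case against.** **The sequence is concealed.** Consent, registration and confirmation of eligibility all precede allocation: "Once patient eligibility is confirmed in REDCap, allocation to either the continuous barbed suturing (CBS) group" or the interrupted group is generated by the system. A reader might infer that concealment is simply not delivered. The documents do not support that. The list is hidden at each enrolment, and what remains is partial deduction from past assignments. This objection stands against the absolute reading. It does not rescue the claim that automation *ensures* concealment.

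**The percentages are ceilings.** Staff would have to know or infer an unstated size and separate four interleaved sequences averaging about 18 patients each. An article may well leave to the full protocol whether the size is withheld from sites, so disclosure cannot be presumed. This stands: the realised share is lower by an amount the documents cannot give.

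**Other safeguards.** Stratification limits imbalance in BMI category and sex, and other risk factors such as diabetes and previous laparotomy are recorded before surgery and could enter an adjusted sensitivity analysis. It would therefore go too far to say that analysis can do nothing about such selection. Selection on unrecorded features would remain. Blinded CT reading guards against biased assessment, not against biased entry, and intention-to-treat analysis keeps whatever selection occurred.

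**Who selects patients.** The documents do not say that the operating surgeons choose whom to approach. The only route they state is the investigator's discretionary exclusion.

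**The remedy is partial.** Varying the block size hardly changes average guessability. This stands and limits what the fix can claim.

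**Conclusion.** The point holds as a weakness in a choice the article states openly. Open label, institution strata and a fixed block size together leave some upcoming allocations deducible, and the sentence claiming that the automated process ensures concealment is stronger than the design supports. This part follows from the text alone.

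The size is conditional. At most 20% to 50% of allocations are expected to be certain in advance, for block sizes from 8 down to 2, and only if site staff know or infer the size and track their strata. The documents give no evidence that any of this has happened or that the size is disclosed, so neither the realised predictability nor any resulting bias can be quantified. The change is worth making because it is cheap and because selection at entry is hard to correct reliably afterwards.

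**What to change.** Replace the fixed block with permuted blocks of randomly varying size, for example 4 and 6, generated by the data centre for each stratum and withheld from site staff. The sizes chosen should not be published while the trial is recruiting. If enrolment has begun, let the block in progress in each stratum run out and apply the varying sizes to new blocks only.

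Reword the concealment sentence to describe what is done, for example: allocation is generated centrally in REDCap after eligibility is confirmed, in blocks of randomly varying size not disclosed to sites, which conceals the sequence and limits prediction of upcoming assignments.

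The cost is a regenerated allocation table, a minor amendment through the Certified Review Board and the hospital review boards, and slightly looser balance within strata. The sample size and the primary analysis do not change.

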### Interventions

In this trial, IS will be compared with CBS. In the IS group, PDS Plus, 45 cm, CTB-1 needle, size 0 will be used with bite widths of 8 mm and suture spacing of 8 mm. In the CBS group, STRATAFIX Symmetric PDS Plus, 45 cm, CTB-1 needle, size 1 will be used with bite widths of 5 mm and suture spacing of 5 mm (Fig. 2). In both groups, wound length will be measured prior to fascial closure, after which suturing will be performed. In the IS group, the number of sutures used will be counted. In the CBS group, the remaining suture length will be measured, and the suture length used for fascial closure will be calculated. In the CBS group, a SL:WL ratio (SL: WL) of 4:1 will be targeted.

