## Objective

The objective of the HIBISCUS trial is to compare CBS with IS performed using a monofilament suture. The overall aim of this study is to reduce the incidence of IH, which is one of the most common complications after abdominal surgery. We hypothesize that CBS will significantly decrease the rate of IH, thereby reducing patient morbidity, improving quality of life, and substantially lowering healthcare costs.

The primary endpoint is the incidence of IH within 18 months after surgery, primarily assessed using scheduled abdominal CT imaging performed at predefined follow-up time points in all patients, with clinical examination serving as a complementary assessment. Secondary endpoints include fascial closure time, postoperative complications (particularly SSI), postoperative wound pain, and the rate of reoperation or readmission.

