### Statistical analysis

Continuous variables will be summarized as mean ± standard deviation (SD) if approximately normally distributed, and as median with interquartile range otherwise; categorical variables will be presented as counts and percentages. Baseline characteristics will be evaluated descriptively without formal hypothesis testing, in accordance with standard recommendations for randomized controlled trials, which discourage statistical testing of baseline variables. All analyses will be performed according to the intention-to-treat (ITT) principle.

For comparisons between groups, t-tests or Mann–Whitney U tests will be applied to continuous variables depending on the distribution assessed using the Kolmogorov–Smirnov test with Lilliefors correction. Categorical variables will be compared using chi-square tests or Fisher’s exact tests, as appropriate.

The primary endpoint of this RCT is the incidence proportion of IH at the mini-laparotomy site. Differences between groups will be evaluated using a two-sided chi-square test for proportions with a two-sided significance level of 5%, based on the prespecified hypothesis that CBS reduces the risk of IH compared with IS. The primary analysis population will include all randomized participants according to the ITT principle. A per-protocol set (PPS) analysis will be conducted as a sensitivity analysis including those who complete the allocated intervention according to the protocol.

Secondary endpoints—including intraoperative outcomes, early postoperative outcomes, the incidence of intraoperative complications, and readmission within 90 days after surgery—will be summarized descriptively for each group.

For the primary endpoint analysis, the incidence proportion of IH during the follow-up period and the corresponding 95% confidence intervals will be calculated for each group. In addition, the odds ratio and 95% confidence interval for IH incidence in the CBS group relative to the IS group will be estimated.

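### Fascial closure time: the planned analysis uses neither the stratification factors nor the wound length measured before closure, which costs precision but does not bias the comparison

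*Protocol article*

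**What the plan says.** The Objective section of the protocol article makes closure time a secondary endpoint: "Secondary endpoints include fascial closure time, postoperative complications (particularly SSI), postoperative wound pain, and the rate of reoperation or readmission". The list of secondary outcomes repeats it.

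The Interventions section fixes stitch spacing at 8 mm in the interrupted arm and 5 mm in the continuous barbed arm, and states for both groups that "wound length will be measured prior to fascial closure, after which suturing will be performed". The operative data list includes both incision length and closure time.

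Randomisation is stratified by institution, BMI group and sex, not by incision length.

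The Statistical analysis section contains two statements that could govern closure time. The general one is that "t-tests or Mann–Whitney U tests will be applied to continuous variables depending on the distribution"; it names no covariate. The specific one begins "Secondary endpoints—including intraoperative outcomes, early postoperative outcomes" and ends by saying that these endpoints "will be summarized descriptively for each group".

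**The concern.** With spacing fixed, a wound of length L mm needs roughly L/8 interrupted stitches or L/5 continuous passes, so the amount of suturing rises in proportion to length within each arm. It is reasonable to expect closure time to rise with it. Length is recorded in everyone immediately before the timed step, yet neither analysis statement uses it. Nor does either use the stratification factors, although a comparison after stratified randomisation would normally account for them.

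What is at stake is the width of the confidence interval for a secondary endpoint, and the power to detect a modest difference in closure time. A second, smaller matter is that the two statements leave open whether closure time is formally compared at all.

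**Working it through.** **The plan's own figure.** The article gives no standard deviation, target difference or power for closure time, so there is no figure on this endpoint to reproduce. Its sample size concerns hernia incidence. For 11.5% versus 3.9%, two-sided 5% and 80% power, the pooled two-proportion formula gives 192 per group, as stated. This point does not touch that figure.

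**Inputs.**
- Patients per arm: 422 / 2 = 211. Closure time is recorded at surgery, so later dropout should not reduce this number.
- Two-sided 5% level and 80% power, used here only to express precision; z values 1.96 + 0.84 = 2.80.
- r, the within-arm correlation of length and closure time on the analysis scale. It is not in the documents; 0.3, 0.5 and 0.7 are assumed.

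**Unadjusted comparison, in SD units of closure time.**
- Standard error = √(2/211) = 0.097.
- Difference detectable with 80% power = 2.80 × 0.0974 = 0.273 SD.

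**With adjustment for length.** Residual variance is multiplied by 1 − r², the standard error by √(1 − r²), and the equivalent number of patients by 1/(1 − r²). Power for a difference d is Φ(d/SE − 1.96).

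| Assumed r | Variance cut (r²) | SE factor | Equivalent patients | Detectable difference (SD) | Power for 0.2 SD |
|---|---|---|---|---|---|
| unadjusted | 0 | 1 | 1 | 0.273 | 54% |
| 0.3 | 9% | 0.954 | 1.10× | 0.260 | 58% |
| 0.5 | 25% | 0.866 | 1.33× | 0.236 | 66% |
| 0.7 | 49% | 0.714 | 1.96× | 0.195 | 82% |

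For a 0.5 SD difference, power is at least 99.9% with or without adjustment.

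**Does chance imbalance in length mislead?** The part of the unadjusted difference that comes from chance imbalance has 95% limits of ±1.96 × r × 0.0974: about ±0.06, ±0.10 and ±0.13 SD for the three values of r. That variation is already part of the standard error of 0.097. A simulation (20,000 runs, 211 per arm, no treatment effect) gave these type I errors:

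| r | Unadjusted | Length-adjusted |
|---|---|---|
| 0.5 | 5.15% | 5.09% |
| 0.7 | 5.04% | 5.18% |

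Both analyses hold the nominal 5%.

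**Stratification factors.** The documents give nothing from which the gain from adjusting for institution, BMI group and sex could be calculated, so no figure is offered.

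**The case against.** **Closure time may never be tested.** The statement on secondary endpoints points to a descriptive summary, and the t-test sentence is generic. This stands in part: one cannot say that the plan fixes an unadjusted test for this endpoint. But a descriptive summary by group ignores length and the strata just as a test would, and the two statements still need reconciling.

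**Covariate adjustment belongs in the analysis plan, which is not shown.** An adjusted supportive analysis may indeed exist there. The article does, however, name methods, and those it names are unadjusted, so the comment is on a stated choice.

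**Length is not a baseline covariate.** The study calendar places allocation before surgery and the trial is open-label, so the incision may be made with the arm known. This stands. A length-adjusted estimate is sound only if the incision is made without regard to arm, and it should not be the lead result.

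**Stronger readings a reader might infer.** One is that a chance difference in length would pass for an effect of technique. The calculation does not support this, because the unadjusted test keeps its error rate. Another is that conversions to open surgery would distort the result through outliers. The article gives no conversion rate, and it provides a rank-based test for non-normal data. A third is that length is the main determinant of closure time. No passage says so; only a positive link follows from the fixed spacing.

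**Conclusion.** The point holds as a minor one about precision on a secondary endpoint. Neither analysis statement uses the stratification factors or a plausible predictor of closure time that is already collected in both arms. The avoidable residual variance is 9% to 49% for correlations of 0.3 to 0.7. That range rests wholly on the assumed correlation, on 211 patients per arm with a recorded time, and on incision length being unaffected by allocation.

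The gain has practical weight only for differences of about 0.2 to 0.3 SD; a large difference would be detected either way. The unadjusted comparison is valid, and the primary endpoint and sample size are unaffected.

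**What to change.** 1. In the Statistical analysis section, state whether closure time is formally compared or only described, so that the two sentences no longer compete.
2. Make the main estimate the between-arm comparison without length, adjusted for institution, BMI group and sex.
3. Add a supportive linear model of log closure time on arm, log incision length and the same strata. Report the ratio of geometric mean times with its 95% confidence interval. Fitting the main estimate on the log scale too would let the two be read side by side.
4. Report incision length by arm, and state the assumption that the incision is made without regard to allocation. If length differs materially between arms, interpret the length-adjusted result with caution.

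The cost is a few sentences and two regressions. No new data are needed, and the change should be made before the data are analysed.
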